#### Blood sampling

The collection of peripheral blood is scheduled throughout the clinical trial as described in Fig. 2.

**Fig. 2 Fig2:**

Clinical study overview

An overview of the trial intervention is presented in Table 1.

**Table 1 Tab1:** Trial interventions

**Trial period**	**Screening Phase**		**Intervention Phase**								**Surgery Phase**		**Follow-up**	**Discontinuation**	
Treatment Cycle/Title:	Pre-screening	Main Study Screening	Radio-immunotherapy					Immunotherapy			Prior to surgery	Surgery	Follow-up	Baseline	Follow-up
**Visits**	**1**	**2**	**3**	**4**	**5**	**6**	**7**	**8**	**9**	**10**	**11**	**12**			
Scheduling Window (Days):	-28 to -7	-7 to 0	1	2	3	4	5	22	43	64	65–85 (+ 28 days)	85 (+ 28 days)		At time of event	Every 12 weeks
Radiotherapy			R1	R2	R3	R4	R5								
Pembrolizumab			C1					C2	C3	C4					
Tissue collection		Biopsy										Surgical specimen			
Immunomonitoring in blood		T1			T2				T3		T4		Fn	Dn	Dn + 1

### Statistical analysis

The primary outcome of this study is pCR. The pCR rate, defined as the absence of residual invasive disease in the rectum and in the lymph nodes at the completion of the neoadjuvant treatment [24], reaches 12–16% in patients receiving treated with SCPRT with delayed surgery or CRT, respectively [5]. Remarkably, induction CT before CRT and surgery increase pCR to 30%-35% [25]. Our hypothesis is that the our sttudy intervention results in a pCR rate that is superior to that of SCPRT. The null hypothesis assumes a 10% pCR rate, and the alternative a 30% pCR rate, which at the usual alpha (0.05) and beta (0.2) cutoffs, require a population of 25 patients, using an exact binomial sample size calculation. The null hypothesis will be rejected if at least 6 patients out of 25 meet the primary endpoint.

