## Method and design

### Hypothesis

We hypothesize that combining pembrolizumab with SCPRT can increase the histological response compared to the standard of care (RT alone) due to the increased immune infiltrate in the tumor (specifically CD8^+^ T cell and FOXP3^+^ T cell) in subjects with localized MSS and MSI RC.

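### The 10% null lies below the 12% pCR rate the protocol itself cites for SCPRT, so exactly 6 of 25 would reject the null without showing superiority to SCPRT

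*Protocol article*

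**What the plan says.** All the design statements stand in one paragraph of the protocol article, under Statistical analysis.

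- Endpoint: "The primary outcome of this study is pCR".
- Historical rates: pCR "reaches 12–16% in patients receiving treated with SCPRT with delayed surgery or CRT, respectively". The wording pairs the figures with the treatments in order, so 12% belongs to SCPRT with delayed surgery and 16% to CRT.
- Claim: the intervention "results in a pCR rate that is superior to that of SCPRT". The Hypothesis section has the same comparator: the combination "can increase the histological response compared to the standard of care (RT alone").
- Test: "The null hypothesis assumes a 10% pCR rate, and the alternative a 30% pCR rate", "at the usual alpha (0.05) and beta (0.2) cutoffs".
- Size: these assumptions "require a population of 25 patients, using an exact binomial sample size calculation".
- Decision: "The null hypothesis will be rejected if at least 6 patients out of 25 meet the primary endpoint".

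The design is single arm (Study design). The patients receive SCPRT followed by delayed surgery (Surgery; Discussion).

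**The concern.** In a single-arm trial the null rate is the only control, so its value decides what a positive result means. Here the claim is superiority to SCPRT, and the only SCPRT rate in the document is 12%, for the same radiotherapy schedule with delayed surgery. The null is two percentage points lower, and the paragraph does not say why.

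The shift favours a positive result. Rejecting 10% shows that the pCR rate is above 10%. It does not by itself show that the rate is above what the protocol says SCPRT achieves. What is at stake is the interpretation of a result at or near the cut-off: the null could be rejected, and the result read as superiority to SCPRT, when the data do not exclude the cited SCPRT rate at the stated error level.

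**Working it through.** **Inputs**, all from Statistical analysis: n = 25, cut-off r = 6, p0 = 10%, p1 = 30%, alpha 0.05, beta 0.2, cited SCPRT rate 12%.

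**Formula.** With X the number of pCRs among n patients, P(X ≥ r | p) is the sum over k = r, …, n of C(n,k) p^k (1−p)^(n−k). Type I error is this tail at the null rate; power is this tail at 30%.

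**Step 1: reproduce the plan.** Sidedness is not stated, so both readings were tried.

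- Upper tail 0.05, 10% against 30%: at n = 25, P(X ≥ 5 | 0.10) = 0.098 is too large and P(X ≥ 6 | 0.10) = 0.0334 is acceptable, so the cut-off is 6. Power is P(X ≥ 6 | 0.30) = 0.8065. With 24 patients and cut-off 6, power is 0.7712, below 0.80. The smallest design is therefore 25 patients with cut-off 6, as stated.
- Upper tail 0.025 (two-sided 0.05): the smallest design is 29 patients with cut-off 7.

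The plan's figures thus match a one-sided test at 0.05, and they are correct for that test.

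**Step 2: the same rule against the cited SCPRT rate.**

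| True rate | P(X ≥ 6 of 25) | P(X ≥ 7 of 25) |
|---|---|---|
| 10% | 0.0334 | 0.0095 |
| 11% | 0.0499 | 0.0156 |
| 12% | 0.0709 | 0.0243 |
| 30% | 0.8065 | 0.6593 |

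Solving P(X ≥ 6 | p) = 0.05 gives p = 0.1101. The 6-of-25 rule holds a one-sided 0.05 only for null rates up to about 11.0%. At 12% the error is 7.1%, which is 0.0709 − 0.05 = 0.0209 above the stated level.

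**Step 3: what each result excludes.** The one-sided 95% exact (Clopper-Pearson) lower limit for x of 25 is the 5% quantile of a Beta(x, 25 − x + 1) distribution.

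- 6/25 (24%): 5% quantile of Beta(6, 20) = 11.0%. Excludes 10%, does not exclude 12%.
- 7/25 (28%): 5% quantile of Beta(7, 19) = 13.9%. Excludes both.

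Only one outcome is affected, exactly 6 of 25. Its probability is 0.0709 − 0.0243 = 0.0466 if the true rate is 12%, and 0.8065 − 0.6593 = 0.1472 if it is 30%.

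**Step 4: what a test against 12% would require.** At n = 25 the smallest cut-off with a one-sided error of at most 0.05 is 7 (2.4%), and power at 30% is then 65.9%. To keep both the stated alpha and the stated power for 12% against 30%, the smallest design is 33 patients with cut-off 8 (type I error 0.0379, power 0.8178).

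**The case against.** The strongest defence is that the paragraph attaches alpha to a 10% null and does what it says. That stands. The sample size and cut-off are right for 10% against 30%, and nowhere does the text claim an error of 0.05 against 12%. A reader might infer an arithmetic error or a false statement of alpha; the document contains neither. The fault is that the null does not match the stated hypothesis.

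Second, the 12% is a single cited figure whose precision and case mix the document does not give, and the verb used with it could be read as an upper figure. This also stands in part: the 7.1% is conditional on a true SCPRT rate of 12%, and at any rate up to about 11.0% the rule keeps to 0.05. But the protocol gives no lower SCPRT rate, so nothing in it supports 10%.

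Third, the gap is small and touches one outcome only. That is true and limits the weight of the point. A reader might instead take the cited CRT rate of 16%, at which the rule rejects with probability 20.0%, as the measure of the problem. The documents do not support that, because both statements of the hypothesis name SCPRT or radiotherapy alone as the comparator, not CRT.

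Finally, the unstated sidedness does not rescue the rule. If 0.05 were meant as two-sided, the upper tail of 3.3% would exceed 2.5% even at the 10% null.

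**Conclusion.** The null and the stated hypothesis are not aligned, and the protocol gives no reason. If the SCPRT rate is the cited 12%, the at-least-6 rule has a one-sided type I error of 7.1% against SCPRT instead of at most 5%, and a result of exactly 6/25 would reject the null without excluding 12%. Seven or more responders would exclude it.

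The conclusion rests on three things: a one-sided test (the only reading that reproduces 25 patients), the 12% taken at face value as a fixed benchmark, and all 25 patients counted in the denominator. It would be going too far to infer that the design is invalid or that the trial must be enlarged. The rule remains a correct test of 10%; what it cannot carry at 6/25 is the claim of superiority to SCPRT.

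**What to change.** Revise the Statistical analysis paragraph as follows.

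1. Keep n = 25 and at least 6 responders as the rule for rejecting a 10% pCR rate. State that the test is one-sided, with type I error 3.3% at 10% and power 80.7% at 30%.
2. State that the same rule has a one-sided type I error of 7.1% against the cited SCPRT rate of 12%.
3. Claim superiority to SCPRT only if the one-sided 95% exact lower limit exceeds 12%, that is, with at least 7 of 25 (type I error 2.4% at 12%, power 65.9% at 30%).
4. Give the reason for the 10% null, if there is one, next to the 12% figure.

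No extra patients are needed. The cost is candour: for the SCPRT claim, either the stated error rate rises to 7.1% or the power at 30% falls by 80.7 − 65.9 = 14.8 percentage points, below the planned 80%. Holding both alpha 0.05 and 80% power against 12% would take 33 patients, 8 more than planned. The Discussion describes the trial as open, so the wording should be settled before pCR results are examined.

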## Discussion

Currently, the standard of care for localized RC consists of neo-adjuvant treatments such as long-course CRT or SCPRT. Both treatments have been shown to increase local control and pCR compared to surgery alone. Contrary to dMRR/MSI-H tumors, novel cancer immunotherapies have shown little clinical impact on MSS CRC. Therefore, the Food and Drug Administration (FDA) granted approval for the use of such ICIs exclusively in the first- and second-line treatment of unresectable or metastatic dMMR/MSI-H CRCs. Remarkably, on top of the direct cytotoxic effects on tumor cells, RT is able to reprogram the TME to exert a potent anti-tumor immune response, thus providing a window of opportunity for immune-modulation. Recently, the first combined approach associating CRT with immunotherapy (Nivolumab) in the VOLTAGE trial [NCT02948348] was shown to be safe, and yielded promising results (30% pCR) in the treatment of MSS RC, but similar combinations (such as SCPRT with ICIs) have never been tested on RC.

This project investigates a novel combination treatment strategy for the treatment of localized RC. Specifically, we will study the clinical and biological impact of combining immunotherapy (pembrolizumab) with SCPRT in the neo-adjuvant treatment of localized MSS and MSI RC. This phase II non-randomized clinical trial is currently open and will recruit 25 patients that will be treated with SCPRT (5 Gy × 5 consecutive days) and four injections of pembrolizumab followed by delayed surgery (NCT04109755). The study primary outcome is pCR evaluated in conjunction with TRG, which is assessed by the Mandard regression grade score. Secondary outcomes include tolerability, safety, survival responses and immune and cellular dynamics in the tumor and in the peripheral blood. We postulate that RT will induce immunogenic cell death followed by inflammation, neoantigen release, reprogramming of the TME, resulting in elicitation of adaptive antitumor immune responses. These immune responses, mediated by tumor specific T cells, will be further amplified by the addition of the immune checkpoint inhibitor pembrolizumab. Upon combination treatment, we anticipate an increase of CD3^+^, CD8^+^ and FoxP3 + T cells in the TME, a dynamic change of the immune cell populations in the peripheral blood and an increased tumor regression as compared to historical controls due to the increased immune infiltrate within the tumor. Our clinical trial will generate important clinical data on the safety and efficacy of the combination and an invaluable insight into immunological changes linked to this combined modality.

## Data Availability

The datasets used and/or analyzed in the current study are available from the corresponding author on reasonable request.

## Abbreviations

CRT: Chemoradiotherapy
CT: Chemotherapy
ctDNA: Circulating tumor DNA
CT: Computed tomography
CTLA-4: Cytotoxic T lymphocyte-associated protein 4
dMMR: Deficient mismatch repair mechanisms
DMFS: Distant metastasis-free survival
ECOG: Eastern co-operative oncology group
EUS: Endoscopy ultrasound
ICI: Immune checkpoint inhibitor
IV: Intravenously
LRRFS: Locoregional relapse-free survival
MRI: Magnetic resonance imaging
MSI: Microsatellite instability
MSS: Microsatellite stable
OS: Overall survival
pCR: Pathological Complete Response
PBMC: Peripheral blood mononuclear cell
PTV: Planning target volume
PD1: Programmed cell death 1
PD-L1: Programmed cell death ligand 1
PFS: Progression free survival
RT: Radiotherapy
RC: Rectal Cancer
Tregs: Regulatory T cells
SCPRT: Short-course preoperative radiotherapy
TME: Tumor microenvironment
TIL: Tumor-infiltrating lymphocyte
TRG: Tumor regression grade
VMAT: Volumetric-modulated arc therapy
